### Recruitment and screening

Trial recruitment will begin in August 2023 and will continue until the required sample size is achieved. This study will utilise an online recruitment strategy targeting parents/guardians of children aged 10 to 12 years as this recruitment method has been established to recruit parents and young people [22]. Study advertisements will be published on the Black Dog Institute’s website and social media channels (Facebook, Instagram, and Twitter) and through Institute communications via established professional newsletters. Paid advertisements will be utilised on social media sites targeting parents (Facebook, Instagram, Twitter, LinkedIn) and Google. The research team will also send two email invitations to adults who have consented to be contacted about research studies conducted at the Institute. Additionally, the research team will contact primary schools via email to share study information with their communities. Contact will also be made by the research team to relevant Australian mental health organisations and services including psychology clinics and parent and youth groups to request distribution of study advertisements through these organisations’ communication channels (e.g., website, newsletters, social media, in-person clinics). Study advertisements will contain a URL directing all interested participants to the study’s webpage where they can review study information, and may choose to commence screening, and provide consent using the provided links. Direct contact between the participant and the study team is not required during recruitment and study enrolment. Parents will complete screening on behalf of the child participant. To ensure participant safety during recruitment and screening, parents of excluded participants will be provided with contact information for Australian mental health and crisis support services and encouraged to seek help if mental health support is required for either themselves or their child. Tips about healthy sleep will also be provided.

### Randomisation

Randomisation to one of the two trial conditions, stratified by gender (male, female, gender diverse) will occur immediately after completion of the baseline survey using a computerised randomisation procedure within the Qualtrics platform and will be carried out according to the International Council for Harmonisation guidelines [51]. Randomisation will be fully automatic, with no input from the research team.

### Blinding

Regarding participant blinding, all study materials will refer to the interventions being examined as “activities to improve sleep” to conceal Sleep Ninja being the smartphone app used in the trial. This is to prevent participants allocated to the control condition from accessing the Sleep Ninja smartphone app, which is publicly and freely available for download in Australia, during their participation in the trial. While participants will be aware of which activity or information they will be required to use (due to the PISCF and instructions for use provided), they will not be directly informed of their condition allocation (i.e., intervention vs. control) to prevent biases in reporting related to expectancies.

The statistician involved in examining the effects of the conditions of primary and secondary outcomes will not be informed of participants’ specific intervention allocation. Condition allocated will be marked as “Condition A, Condition B” to ensure the statistician remains blinded to participants’ intervention upon primary and secondary analysis of the results. All other potential markers of allocation will be removed from the data analysis file. Upon completion of these analyses, the statistician will be become unblinded when examining mediators and moderators as well as intervention completion rates. This data will only be reviewed by the trial statistician upon completion of the primary and secondary outcomes.

The Chief investigators, trial manager and research assistants will be unblinded to participants’ allocation as they will have access to the Qualtrics data to contact participants if they experience adverse events (see Monitoring below for more information). They will also be responsible for downloading and cleaning the data extracted. The Chief Investigators, Trial Managers, Data Analyst and Research Officers/Assistants will not be involved in data analysis of the primary and secondary outcomes.

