### Hypotheses

The primary hypothesis is that relative to the active control condition, participants who receive the Sleep Ninja app will show greater improvements in child-reported insomnia symptoms at 6-weeks post-baseline (primary endpoint). Secondary hypotheses include that relative to the control condition, participants who receive the Sleep Ninja app will show a greater reduction in symptoms of depression and anxiety, daytime sleepiness, and improved sleep quality at 6-weeks post-baseline (primary endpoint), and improvements in primary and secondary outcomes will be maintained at 3-months post-baseline. In line with previous studies, it is hypothesised that reductions in depressive symptoms will be mediated by improvements in insomnia symptoms. The number of MDD cases at 9-months post-baseline in both groups (tertiary endpoint) will be explored.

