### Measures of mechanisms

All potential mechanisms will be measured at all four assessments (baseline, primary, secondary, and tertiary endpoints) and explored as mediators of change.

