### Data collection, management, and statistical methods

Participant data will be collected and securely stored on the University of New South Wales (UNSW) OneDrive which are hosted on servers provided by the UNSW at GovDC Data Centres in Sydney, Australia. The data is stored in a SQL Server 2016 database, which undergoes daily backups and is supported by 128-bit encryption. To ensure participant confidentiality, at the data analysis stage, each participant will be assigned and only identified by a unique identification code.

For analyses, all study data will be exported from the Qualtrics Survey Platform to SPSS Version 26 using a Microsoft Excel file format. Files with identifiable data will be stored on UNSW OneDrive and once deidentified by authorized members of the research team for analysis will be stored on a secure sever. Any personally identifiable information, such as participant names, email addresses, mobile phone numbers, IP addresses, free response data, will be removed from the outcomes analysis file. Only the research team listed on the project will have access to identifiable study assessment data, while aggregate deidentified data will be retained for future evidence synthesis.

Analyses will be conducted to determine the effect of the interventions on insomnia symptoms at the primary and secondary endpoints. Analyses will be undertaken on an intention-to-treat basis, including all participants randomised, regardless of the intervention received. The effectiveness of the trial intervention will be established using mixed-model repeated measures (MMRM) analyses due to the inclusion of participants with missing data with this approach. The primary hypothesis will be evaluated by a contrast evaluating change in child-reported insomnia symptoms between baseline and 6-weeks post-baseline (primary endpoint), based on the interaction between time and condition. The same approach will be used for secondary outcomes. Adherence and acceptability of the intervention will be described.

Exploratory analyses will compare proportion of young people who meet criteria for MDD at the tertiary endpoint, as well as those showing significant symptoms of depression, operationalised as a t-score of greater than 65 on the RCADS.

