To determine whether improvements in depression are mediated by changes in sleep, an additional MMRM analyses will be conducted using depression symptoms as the outcome and including a 3-way interaction term (time × group × insomnia). Similarly, to explore other potential mediators of treatment effects, additional MMRM analyses will be used and include 3-way interaction terms (time × group × mediator).

A deidentified data set may be requested by emailing the study team. Release of the data will be decided on a case-by-case basis and at the discretion of the Chief Investigator and facilitated through a data repository using Research Data Australia.

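### The statistician is unblinded before the mediator and moderator analyses, although the planned models run on A/B codes, and it is unclear whether masking covers the 9-month MDD comparison

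*Protocol article*

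**What the plan says.** The Blinding section labels the arms Condition A and Condition B and strips other markers of allocation from the analysis file, "to ensure the statistician remains blinded to participants’ intervention upon primary and secondary analysis of the results". When those analyses are finished, "the statistician will be become unblinded when examining mediators and moderators as well as intervention completion rates". On the order of work it adds: "This data will only be reviewed by the trial statistician upon completion of the primary and secondary outcomes".

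The Hypotheses section includes a mediation hypothesis: "it is hypothesised that reductions in depressive symptoms will be mediated by improvements in insomnia symptoms". The statistical methods section tests it with a further mixed model for depression that contains a time × group × insomnia interaction. It gives the other mediators the same form, but only to explore them. Under Measures of mechanisms, "All potential mechanisms will be measured at all four assessments".

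On the diagnostic outcome, the statistical methods section says: "Exploratory analyses will compare proportion of young people who meet criteria for MDD at the tertiary endpoint". The same sentence adds the comparison of RCADS t-scores above 65. The article also describes MDD under its Exploratory outcomes heading, but the MDD row of Table 1 stands in the Secondary Outcomes block. The Blinding section mentions neither MDD nor the RCADS threshold.

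**The concern.** The sponsor evidently values a masked analyst, yet the mask comes off for one of the trial's own directional hypotheses. The rule puts mediators and moderators together with completion rates. Completion rates do give a reason to unblind. The planned mediator models do not, as far as the article describes them.

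At stake is the protection against choices that lean, knowingly or not, towards the expected result. Mediation and subgroup work usually leaves the analyst more latitude than the primary contrast. For the hypothesised mediation, the article speaks only of depression symptoms and insomnia. Each has a child and a parent version, and there are three follow-up times, so the wording admits up to 2 × 2 × 3 = 12 variants. A statistical analysis plan may narrow these, and their absence from the article is not itself a fault. Masking is the safeguard for whatever latitude remains.

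**Working it through.** The plan states no figure on this point, so there is none to reproduce. The check asks which analyses need the true labels, and what the masking rule covers.

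**1. Mediator models.** Group enters the planned model as a two-level factor. Let g be 0 or 1, and let the swapped code be h = 1 − g. For time t and mediator m, the three-way term becomes

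β·t·g·m = β·t·(1 − h)·m = β·t·m − β·t·h·m.

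The three-way coefficient changes sign, and the extra β·t·m is absorbed by the time × mediator term. The fit, the standard error and the two-sided p-value stay the same.

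A numerical check used simulated data: 214 participants, two time points, one mediator value each and a random intercept. It illustrates the invariance and does not model the trial.

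| Labelling | Three-way coefficient | p |
|---|---|---|
| As generated | −0.2328 | 0.3056 |
| Arms swapped | +0.2328 | 0.3056 |

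The true labels are needed only to name the direction of the result, which can be done after the analysis is locked.

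**2. Do the mediator data reveal the arm?** Table 1 schedules the insomnia, dysfunctional-belief, pre-sleep anxiety and negative-thinking measures at baseline and all three follow-ups. Its footnote restricts only treatment adherence to the intervention group. Having a mediator measurement therefore does not identify the arm.

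**3. Comparison of MDD proportions.** Fisher's exact test on an invented table (3 of 64 against 6 of 64) gives p = 0.4917 under either labelling. Only the odds ratio inverts: 0.4754 against 2.1034, and 1/0.4754 = 2.1034. A comparison of the proportions above the RCADS threshold has the same two-by-two structure.

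**4. Adherence, usage and completion.** Under Intervention adherence and attrition, the adherence questionnaire goes to the intervention group only. Engagement is recorded as in-app data in one arm and as link clicks to the flyers in the other. These data reveal the arm whatever code is used.

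**5. Moderators.** The article names none. A moderator such as gender or age can be analysed on A/B codes. One built from usage cannot, for the reason in step 4.

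**6. Coverage of MDD and the RCADS threshold.** The masked set is the primary and secondary analyses. Read with the text, which calls both comparisons exploratory, they fall outside it. Read with Table 1, MDD falls inside. The Secondary Outcomes block of Table 1 also holds the mediators and quality of life, which the text classes separately, so its heading is weak evidence either way. Depressive symptoms are a secondary outcome, but the comparison above the threshold is introduced as exploratory. The list of analyses that bring unblinding (mediators, moderators, completion rates) includes neither. Coverage cannot be settled from the article.

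**The case against.** The plan openly states a common sequence: masked confirmatory work, then unblinded explanatory work. The primary and secondary analyses stay masked, and the treatment effects on both insomnia and depression are among them. The form of the mediation model is also fixed in advance. All of this stands, and it keeps the point small.

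Three stronger readings are tempting, and the document does not support them.

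- A reader might infer that masking does not extend to the 9-month MDD comparison. The Blinding section is silent, and the article classifies MDD in two ways. Only unclear coverage can be claimed. MDD also carries no directional hypothesis.
- A reader might infer that none of the unblinded analyses needs the true labels. This is shown for the planned mediator models, but not for moderators, since none is named and a usage-based one would disclose the arm.
- A reader might object that the mediation hypothesis is tested with the primary result already known. That follows from the order of analyses, and A/B coding does not remove it. If one coded arm has clearly improved more, the analyst may also guess which arm is Sleep Ninja, so the protection is weakest when there is an effect to explain.

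The objection does not justify disclosing the labels for models that do not use them.

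**Conclusion.** The point holds as a minor one. The Blinding section discloses allocation before the mediator and moderator analyses because it groups them with completion rates. The planned time × group × mediator models, including the one that tests the hypothesised mediation of depression by insomnia, can be run on A/B codes. Whether masking covers the 9-month MDD and RCADS > 65 comparisons is unclear.

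The stated-hypothesis consequence applies to the insomnia mediation alone. The other mediators are exploratory, and no moderator hypothesis is given. The gain from a change is modest, and the size of any bias cannot be derived from the document. The headline conclusions of the trial are not affected. The verdict assumes that the mediation models are fitted as the article describes, with group as a two-level factor and without usage data as covariates.

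**What to change.** Reword the unblinding sentence so that the A/B code stays in place until these analyses are complete and locked: primary, secondary, mediation, moderators not based on usage, 9-month MDD, and RCADS > 65. Then unblind, and only then run the adherence, app-usage and completion-rate summaries and any usage-based moderator. Naming MDD and the RCADS threshold in the masked set settles their coverage however they are classified. The text and Table 1 should also give MDD the same status.

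The cost is one sentence in the Blinding section and a change in the order of analyses, with no new data, staff or procedure.

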### Data collection, management, and statistical methods

Participant data will be collected and securely stored on the University of New South Wales (UNSW) OneDrive which are hosted on servers provided by the UNSW at GovDC Data Centres in Sydney, Australia. The data is stored in a SQL Server 2016 database, which undergoes daily backups and is supported by 128-bit encryption. To ensure participant confidentiality, at the data analysis stage, each participant will be assigned and only identified by a unique identification code.

For analyses, all study data will be exported from the Qualtrics Survey Platform to SPSS Version 26 using a Microsoft Excel file format. Files with identifiable data will be stored on UNSW OneDrive and once deidentified by authorized members of the research team for analysis will be stored on a secure sever. Any personally identifiable information, such as participant names, email addresses, mobile phone numbers, IP addresses, free response data, will be removed from the outcomes analysis file. Only the research team listed on the project will have access to identifiable study assessment data, while aggregate deidentified data will be retained for future evidence synthesis.

Analyses will be conducted to determine the effect of the interventions on insomnia symptoms at the primary and secondary endpoints. Analyses will be undertaken on an intention-to-treat basis, including all participants randomised, regardless of the intervention received. The effectiveness of the trial intervention will be established using mixed-model repeated measures (MMRM) analyses due to the inclusion of participants with missing data with this approach. The primary hypothesis will be evaluated by a contrast evaluating change in child-reported insomnia symptoms between baseline and 6-weeks post-baseline (primary endpoint), based on the interaction between time and condition. The same approach will be used for secondary outcomes. Adherence and acceptability of the intervention will be described.

Exploratory analyses will compare proportion of young people who meet criteria for MDD at the tertiary endpoint, as well as those showing significant symptoms of depression, operationalised as a t-score of greater than 65 on the RCADS.

To determine whether improvements in depression are mediated by changes in sleep, an additional MMRM analyses will be conducted using depression symptoms as the outcome and including a 3-way interaction term (time × group × insomnia). Similarly, to explore other potential mediators of treatment effects, additional MMRM analyses will be used and include 3-way interaction terms (time × group × mediator).

A deidentified data set may be requested by emailing the study team. Release of the data will be decided on a case-by-case basis and at the discretion of the Chief Investigator and facilitated through a data repository using Research Data Australia.

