**Fig. 1 Fig1:**
[figure not shown]
Participant recruitment and study flow diagram

Parents who would like their child to take part will be directed to the study webpage and will be asked to complete a brief online screening questionnaire on behalf of their child to determine eligibility. Parents of children who do not pass screening will be provided with sleep health information and mental health service information. Only parents of eligible children will be invited to review the online Participant Information Statement and Consent Form (PISCF). Once parental consent is provided, a child-friendly version of the PISCF will be presented with the child’s assent assumed if they progress through and are registered for their trial by their parent. Parents of participants will be asked to register by providing the name of the parent and child, the parent’s email address, and the parent’s mobile phone number. This process has been successfully used in previous trials conducted online [17, 31].

Following registration, the parent and child will be directed to the first (baseline) study assessment, with two reminders sent if not completed (Days 3 and 5). Participants and their parents who fail to complete the baseline assessment within the allocated time will be automatically withdrawn from the study. Upon completion of the baseline assessment, participants will be randomised to one of the two study conditions. Parents of participants will receive an email containing information regarding their child’s allocated intervention (Sleep Ninja or digital psychoeducation flyers). At six-weeks post-baseline, 3-months and 9-months follow-up, all randomised participants will be invited via email and SMS to complete the study assessments.

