### Sample size

The total sample size required for detecting change in the primary outcome at the primary endpoint was calculated to be 214. This was based on using α = 0.05, power = 0.8 to detect a medium between-group effect size (d = 0.41) [17, 22] on child-reported insomnia outcomes. This estimate accounts for an attrition rate of 40% between baseline and the primary endpoint. The effect size parameter used in the power calculation accounts for potential effects of the active control condition, as seen in the adolescent study [17], but is more conservative than the between-group effect size reported in that study (d = 0.41) due to the differences in the delivery format (parent-supported vs. self-directed).

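### The primary change-from-baseline contrast is valid, but fixing a common baseline mean would make it more precise at no cost in data

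*Protocol article*

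**What the plan says.** All references are to the Protocol article. Under Data collection, management, and statistical methods, effectiveness is assessed by "mixed-model repeated measures (MMRM) analyses due to the inclusion of participants with missing data with this approach". The primary hypothesis is evaluated by "a contrast evaluating change in child-reported insomnia symptoms between baseline and 6-weeks post-baseline", "based on the interaction between time and condition". Secondary outcomes are to be handled in the same way. The analysis set is every randomised child.

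On timing, the Procedure and participant timeline section says: "Upon completion of the baseline assessment, participants will be randomised to one of the two study conditions". The Randomisation section agrees: allocation is "stratified by gender (male, female, gender diverse) will occur immediately after completion of the baseline survey".

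Two things are not stated. The article does not say whether the baseline means are free to differ between arms or held equal, and it gives no list of model covariates.

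**The concern.** If the contrast is a change from baseline, baseline is one of the repeated outcomes. The ordinary model with time, condition and their interaction then gives each arm its own baseline mean, and the treatment estimate is the 6-week difference minus the whole of the observed baseline difference.

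That subtraction makes sense when the arms might truly differ at baseline. Here they cannot, except by chance, because allocation comes after the baseline assessment. Unless baseline and 6-week scores are perfectly correlated, removing the full chance difference over-corrects and adds variance. What is at stake is precision on the primary endpoint. The same construction is carried to the secondary outcomes, where the size of the loss depends on each outcome's own correlation and missingness.

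**Working it through.** **The plan's own figure.** The Sample size section gives N = 214 for d = 0.41, α = 0.05 (taken as two-sided), power 0.80 and 40% attrition. The normal-approximation formula gives 2 × (1.960 + 0.842)² / 0.41² = 93.4, so 94 per arm and 188 in total. Dividing by 0.6 gives 313.3, so 314. The stated 214 is not reproduced. That is a separate matter; 214 is used below only as the planned size.

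**Inputs.**
- From the article: equal allocation, so n = 214 / 2 = 107 per arm; 40% attrition to 6 weeks, so m = 0.6 × 107 = 64.2 per arm with 6-week data; d = 0.41.
- Assumed: two-sided 5% test; equal outcome variance at both visits, set to 1; dropout that leaves the model valid; baseline-to-6-week correlation r of 0.3 to 0.8.

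**Formulas.** Variance per arm, by maximum likelihood with baseline known for all n and the 6-week score for m:
- Free baseline means: V_free = (1 − r²)/m + (1 − r)²/n
- Common baseline mean: V_con = (1 − r²)/m

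The second term of V_free is the chance baseline difference carried into the contrast. The constraint removes it. The variance of the treatment contrast is twice the per-arm value, and power = Φ(0.41/√(2V) − 1.96).

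**Example at r = 0.5.** V_con = 0.75/64.2 = 0.01168. V_free = 0.01168 + 0.25/107 = 0.01168 + 0.00234 = 0.01402. The ratio is 0.833, a 17% reduction. Power with free means is Φ(0.41/0.1674 − 1.96) = Φ(0.49) = 69%; with the constraint it is Φ(0.41/0.1529 − 1.96) = Φ(0.72) = 77%.

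| r | V_free | V_con | Variance reduction | Power, free | Power, constrained |
|---|---|---|---|---|---|
| 0.3 | 0.01875 | 0.01417 | 24.4% | 56% | 68% |
| 0.5 | 0.01402 | 0.01168 | 16.7% | 69% | 77% |
| 0.7 | 0.00879 | 0.00794 | 9.6% | 87% | 90% |
| 0.8 | 0.00598 | 0.00561 | 6.2% | 96% | 97% |

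At r = 0.3 the free-means contrast is less precise than comparing 6-week scores with baseline ignored: 0.01875 against 1/64.2 = 0.01558. At r = 0.5 the gain is worth 1/0.833 = 1.20 times the sample, or about 0.20 × 214 = 43 children.

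**Checks.** A four-visit calculation with assumed cumulative dropout of 40%, 45% and 50% gave reductions of 24.4%, 16.7%, 9.6% and 6.2% under compound symmetry, and the same to within 0.1 point under a first-order autoregressive structure. A simulation of 6,000 trials per setting, with no gender effect, gave 22.9%, 16.6% and 10.4% at r = 0.3, 0.5 and 0.7. Without attrition the gains would be larger: 35%, 25%, 15% and 10% at r = 0.3, 0.5, 0.7 and 0.8.

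**Gender.** In the same simulation, adding the three-level gender factor to the constrained model changed the reduction by less than one percentage point: 16.6% to 16.0% at r = 0.5 with no gender effect, and 18.6% to 18.4% with an assumed shift of 0.3 SD. The gain comes from the baseline constraint.

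**The case against.** The strongest reply is that nothing here is wrong. The change contrast is unbiased under randomisation, uses all randomised children, rests on the same missing-at-random assumption as the alternative, and matches a hypothesis worded in terms of improvement. This stands: the point is about efficiency only.

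Next, free baseline means are not explicit text. A constrained model also has baseline among its outcomes and also tests time-by-condition terms, so the wording fits both, and an article may leave this detail to its analysis plan. This stands in part. Free means are the ordinary reading, and the constraint has to be imposed deliberately. If it is already intended, one sentence confirms it.

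Third, the size depends on a correlation that the article does not give. This also stands. At 0.8 the gain is only about 6%.

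A reader might go further in two ways that the article does not support. One is to infer that the model wrongly leaves out the gender stratifier. With no covariate list, the article neither includes nor excludes it, and it has almost no bearing on precision here. The other is to argue that the gain is needed because the stated power is not met. On the figures above, the free-means contrast has 87% power at r = 0.7, over the 80% target, so that claim also depends on the correlation. The mismatch between N = 214 and its stated inputs should be judged separately.

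**Conclusion.** A free improvement. On its usual reading the planned primary contrast is valid but less precise than it could be. Holding the baseline means equal is justified because randomisation follows baseline; it loses no children and, in large samples, is never less efficient. The variance falls by about 24%, 17%, 10% and 6% at r = 0.3, 0.5, 0.7 and 0.8, with power gains of about 12, 8 and 3 percentage points at the first three. These figures assume 107 per arm, 40% attrition, equal variances, d = 0.41 and a two-sided 5% test. The documents show no bias, no inflated type I error and no contradiction in the contrast itself.

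**What to change.** Specify the primary analysis as a constrained longitudinal mixed model: PISI-A at baseline, 6 weeks, 3 months and 9 months; a time effect; condition-by-time terms for the post-baseline visits only, so that both arms share one baseline mean; and an unstructured covariance matrix. Name the condition difference at 6 weeks as the primary test. Use the same model for the continuous secondary outcomes, at the visits where each is measured.

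State also whether gender is a covariate. Including it is optional good practice because it is the stratification factor; if it is included, give a rule for pooling the gender-diverse stratum should it be very small.

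The cost is a few sentences in the analysis plan, with no new data or participants. The choice should be recorded before outcomes are analysed by condition, so that it cannot depend on the observed baseline difference.
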